#### Secondary Outcomes

Secondary outcome measures will include assessment of upper-body muscle strength (measured through isometric bench press; same equipment used for primary outcome), handgrip strength (Jamar, Patterson Medical, Illinois, USA) (69), cardiopulmonary fitness/vo2 peak [through Cardiopulmonary Exercise Test (Cortex, Leipzig, Germany)], walking distance (6-min Walk Test) (70), lower extremity muscle strength and endurance (through 30-s and 1-min Sit-to-Stand Test, respectively) (71, 72), basic functional mobility (through Timed up-and-Go test) (73), body composition [through Whole-Body Dual-Energy X-ray Absorptiometry (DXA) Scan (Lunar, Lunar Corporation Madison, WI, USA)], and quality of life (through PedsQL Generic Core Scale) (74). These outcomes represent direct or surrogate measures of physical fitness, physical function, or quality of life. Each outcome is described in detail at the uploaded protocol at clinicaltrails.gov (NCT04706676).

Further, as a measure of the economic cost of hospitalization, total days of hospitalization will be measured and compared in the two groups after ended treatment.

#### Explorative Outcomes

On an explorative basis, this study will measure neuropathy (through Pediatric Modified Total Neuropathy Score) (75), balance (as Modified Clinical Test of Sensory Interaction in Balance) (76), physical activity and sedentary time through accelerometry (ActiGraph™, ActiGraph LLC, Pensacola FL, USA), muscle power through countermovement jump (FP4, HUR-Labs Oy, Tampere, Finland), markers of dysmetabolism (metabolomics, intestinal microbiota, inflammatory cytokines and mediators, growth and reproductive factors, and macro- and micronutrients collected through plasma, urine and feces samples, and dietary assessment), self- and proxy-reported general physical activity, health-related quality of life (PedsQL 3.0 Cancer Scale) (74), and fatigue (PedsQL Multidimensional Fatigue Scale) (74).

To further measure the potential cost of standard care/rehabilitation, the total number of physio- and occupational therapy treatments will be measured and compared between groups and centers.

### Sample Size

A 10% increase in muscle strength due to physical exercise is regarded as a clinically relevant change (62). Based on a mean 41.4 ± 7.6 (lower body muscle strength, kg ± SEM) (44) and a 10% increase, an alpha level of 0.05, and power of 80%, 106 children are needed. We expect that approximately 60 children with cancer aged 6–17 will be diagnosed per year at Copenhagen University Hospital, Rigshospitalet, Aarhus University Hospital, and Odense University Hospital. Assuming a 20% dropout rate, 2.2 years will be required to include the needed number of children with cancer (*n* = 127).

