### Randomization

Following baseline assessment, participants will randomly be assigned to either the intervention group (integrative neuromuscular training + motivational-counseling sessions + usual care) or active control group (home-based training program + motivational-counseling sessions + usual care) by a blinded statistician using a computer-generated concealed allocation procedure to secure a proportionate stratified random sample with a (2:2) allocation. Participants will be stratified by sex, pubertal stage, and diagnosis as treatment for (1) solid tumors, (2) CNS-tumors, and (3) treatment for hematologic malignancy.

Baseline assessors and the statistician will be blinded to the allocation of participants; however, due to the nature of the intervention, neither participants nor intervention staff will be blinded throughout the intervention.

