### Statistical Considerations

Constrained longitudinal data analysis is applied to evaluate the intervention effectiveness by using constrained (generalized) linear mixed models in two scenarios. In the first one, predictors will include follow-up time points categorized as 3 and 6 months to account for any non-linear effect and dummy variables representing the intervention group at 3- and 6-month follow-ups, respectively. In the second scenario, the time variable will be treated as a continuous variable and an interaction between treatments (binary-coded, 1 representing intervention group), and the time variable will be included instead. Normal distribution will be applied on continuous outcome muscle strength, while binomial distribution will be applied on binary outcome metabolic syndrome. Baseline characteristics, such as age (as a continuous variable), gender, and type of cancer (categorized as solid, CNS, and hematologic tumors), will be included additionally as covariates in both scenarios. Patient identity will serve as a random intercept. Likelihood ratio tests based on maximal likelihood will be applied for the model selection of the fixed effects to determine linear or non-linear associations. Benjamin-Hochberg procedure will be applied to reduce the false discovery rate due to multiple comparisons. The level of significance is 0.05.

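### The sample size labels 7.6 kg as an SEM, but 106 children follows only if 7.6 kg is the between-child SD; the label or the calculation is wrong

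*Protocol article*

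**What the plan says.** The Sample Size section sets the target effect first: "A 10% increase in muscle strength due to physical exercise is regarded as a clinically relevant change". It then gives the one variance figure on which the trial's size rests, taken from a cited study: "Based on a mean 41.4 ± 7.6 (lower body muscle strength, kg ± SEM) (44) and a 10% increase". It concludes with "an alpha level of 0.05, and power of 80%, 106 children are needed". An allowance for dropout brings the total to 127. The section reports no SD, no sample size for the cited study, no conversion from SEM to SD and no correlation between baseline and 6-month strength.

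Two other sections bear on the point. Randomization describes "a proportionate stratified random sample with a (2:2) allocation", which is equal allocation. Statistical Considerations plans a baseline-constrained mixed model with age, sex and cancer type as covariates: "Constrained longitudinal data analysis is applied to evaluate the intervention effectiveness by using constrained (generalized) linear mixed models in two scenarios". The sample size does not refer to that model.

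**The concern.** An SD describes how much children differ from one another. An SEM describes how precisely a mean was estimated, and equals the SD divided by the square root of the number of children in the source sample. A two-group sample size needs the SD. If an SEM is entered in its place, the required number is too small by a factor of about the source sample size.

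Here the text says SEM and the arithmetic behaves as if the figure were an SD. Both cannot be right. The figure supports the power claim for the primary outcome, isometric knee extension strength at 6 months. If the label is right and the calculation wrong, the trial could have much less than 80% power for the difference it calls clinically relevant. A null primary result could then be read as evidence of no effect when the trial had little chance of finding one. If only the label is wrong, a reader is misinformed about the input but nothing else changes.

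**Working it through.** **Inputs**
- Mean 41.4 kg, spread 7.6 kg, 10% effect, alpha 0.05, power 80%: Sample Size section.
- Equal allocation: Randomization section.
- Two-sided testing: not stated there. It is assumed here because it reproduces the stated number.

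**Step 1. Reproduce 106.**

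Difference: 0.10 × 41.4 = 4.14 kg.

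n per arm = 2 × (1.960 + 0.842)² × (SD / difference)² = 2 × 7.85 × (7.6 / 4.14)² = 52.9, rounded up to 53 per arm, or 106 in total.

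This is exactly the stated number. Other routes with the same inputs:
- The two-sample t-test version gives 53.9, so 54 per arm and 108 in total, which is close.
- One-sided testing gives 84.
- A paired one-sample calculation gives about 29.

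So 106 comes from 7.6 kg used as a between-child SD, with no allowance for baseline correlation.

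**Step 2. If 7.6 kg is an SD and the label is wrong.**

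With 53 per arm, power is 80.1% by normal approximation and 79.3% by t-test. The stated size and power stand.

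**Step 3. If 7.6 kg is an SEM and the label is right.**

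SD = 7.6 × √n, where n is the size of the source sample. The article does not give n, so the values below are assumptions. Unadjusted power is from a two-sample t-test with 53 per arm. The detectable difference at 80% power scales with the SD, so it is 10% × √n of the mean. The total needed is from the normal approximation.

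| Assumed source n | SD (kg) | Unadjusted power | Detectable difference | Total N for 80%, unadjusted |
|---|---|---|---|---|
| 2 | 10.7 | 50% | 14% | 212 |
| 5 | 17.0 | 24% | 22% | 530 |
| 10 | 24.0 | 14% | 32% | 1,060 |

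**Step 4. Allow for the planned baseline-constrained model.**

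As an approximation, treat the model as an analysis of covariance on baseline. The SD is then multiplied by √(1 − r²), where r is the correlation between baseline and 6-month strength. The article gives no r, so it too is assumed. At r = 0.8 the multiplier is √(1 − 0.64) = 0.6.

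| Assumed source n | SD × 0.6 (kg) | Power, r = 0.8 |
|---|---|---|
| 2 | 6.4 | 91% |
| 5 | 10.2 | 54% |
| 10 | 14.4 | 31% |

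The correlation that brings power back to 80% with 106 children is √(1 − 1/n): 0.71 at n = 2, 0.89 at n = 5 and 0.95 at n = 10. At n = 5 and r = 0.9, for example, power is about 81%.

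**The case against.** The strongest reply is that this is a slip in one word. The exact match at 106 shows only that the figure was used as an SD, which is what one would see if it is an SD and the label is a mistake. That stands: it is a plausible explanation. Larger source samples make it more so. At an assumed n of 20 the SD would be 7.6 × √20 = 34 kg on a mean of 41.4 kg, and a normal distribution would put about 11% of children below zero on a force that cannot be negative. At n = 30 the SD (41.6 kg) would be as large as the mean.

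The reply does not settle the matter. Read as an SD, 7.6 kg is 7.6 / 41.4 = 18% of the mean, which puts about 95% of children between 27 and 56 kg (41.4 ± 1.96 × 7.6). That is a narrow spread for absolute leg strength in children of both sexes aged 6 to 17.9 years. This is a judgement and not a fact in the article, but it is a reason not to assume the harmless explanation.

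A second reply is that the constrained model recovers power. In part it does: for a very small source sample and a high correlation, 80% is within reach even if the label is right. A reader might therefore infer too much from saying that 80% power holds only if the label is wrong. But the Sample Size section invokes no such correlation and 106 is obtained without one, so the model does not repair the stated calculation.

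A reader might also infer that the trial is underpowered. The article does not support that. It depends on the SD and sample size of the cited study, and neither is given.

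Finally, this is not a matter that an article may leave to a fuller document. It is a contradiction between two things the article does state.

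**Conclusion.** The label and the unadjusted calculation contradict each other in the sole variance input to the sample size. That much is certain from the Sample Size section. Which of the two is wrong cannot be decided from the article.

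The consequence runs from none, if 7.6 kg is an SD, to a substantial loss of power, if it is an SEM. In the second case the size of the loss rests on two assumed quantities, the source sample size and the baseline correlation, and the figures under working illustrate the range and are not estimates for this trial. Underpowering is a possibility to be ruled out, not a demonstrated fault.

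**What to change.** Look up the SD and sample size in the cited source.

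- If 7.6 kg is an SD, change the label to SD. The sample size and power stay as they are.
- If it is an SEM, compute SD = 7.6 × √n and state it. Then restate the power, or the difference detectable with 80% power, that the planned number of children delivers under the baseline-constrained model, and give the assumed baseline correlation with its basis.

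The cost is one look at the source, a recalculation if needed, and corrected wording. No additional patients are called for, though the stated power may become less favourable. As an optional extra, a blinded estimate of the pooled 6-month SD given baseline, from children already enrolled, would supply the relevant variance directly.

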**Methods:**

One hundred and twenty-seven children and adolescents, newly diagnosed with malignant and benign neoplasia, aged 6–17 years, and treated with chemotherapy or radiation will be randomized to either the intervention or the control arm of the study. The intervention group will, in addition to usual care, be offered a combination of 6 months of supervised physical exercise (integrative neuromuscular training) and home-based exercise. The active control group will, in addition to usual care, receive information along an unsupervised written home-based training program. All participants, including parents, will receive information about the importance of physical exercise during the course of cancer treatment, at the start of treatment, and in 5 monthly sessions. The primary outcome is measured in terms of isometric quadriceps muscle strength. Secondary outcomes include muscle strength and endurance, markers of metabolic syndrome and dysmetabolism, exercise capacity, physical function and activity, days of hospitalization, and health-related quality of life. Assessment will be conducted at treatment initiation (baseline), at 3 and 6 months after inclusion, and 1 month and 1 year after ended treatment. The primary endpoint for lower-body muscle strength is at 6 months after treatment initiation. The effects of the intervention will be evaluated through a constrained linear mixed model.

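### The enrolment target of 127 protects the required 106 children against about 16.5% dropout, not the 20% the protocol assumes; 20% requires 133

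*Protocol article*

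**What the plan says.** The Sample Size section takes a 10% difference in muscle strength as the effect to detect ("A 10% increase in muscle strength due to physical exercise is regarded as a clinically relevant change") and draws its mean and spread from an earlier study ("Based on a mean 41.4 ± 7.6 (lower body muscle strength, kg ± SEM"). From these it concludes, for "an alpha level of 0.05, and power of 80%, 106 children are needed". It then expects roughly 60 eligible diagnoses per year across the three centres and continues: "Assuming a 20% dropout rate, 2.2 years will be required to include the needed number of children with cancer", with n = 127 in brackets.

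The Methods paragraph of the abstract carries the same figure forward as the number to be randomized: "One hundred and twenty-seven children and adolescents, newly diagnosed with malignant and benign neoplasia". The Randomization section gives the allocation as 2:2, that is, equal arms.

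The article does not print the formula that leads from 106 to 127, and it states no dropout rate or allowance other than 20%.

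**The concern.** A dropout rate is a fraction of those enrolled. To finish with 106 children after losing 20%, one divides 106 by 0.8. Multiplying by 1.2 instead adds 20% of the completers, which is less than 20% of the enrolled. The stated 127 matches the multiplication and not the division.

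If so, the trial falls below its own required number when attrition is exactly as assumed, and the 80% power claim for the primary endpoint does not follow from the stated target. Since 127 is the headline enrolment figure, the mismatch affects both recruitment planning and the reported power.

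**Working it through.** **Inputs.** From Sample Size: mean 41.4 kg, spread 7.6 kg, relevant difference 10%, alpha 0.05, power 80%, required number 106, dropout 20%, target 127, about 60 diagnoses per year. From Randomization: equal allocation. Two readings are assumed because they reproduce the protocol's figure: the test is two-sided, and 7.6 is used as a standard deviation although it is labelled SEM.

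**Step 1. Reproduce the 106.** The difference is 0.10 × 41.4 = 4.14 kg. By the normal approximation, the number per arm is

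n = 2 × (1.960 + 0.842)² × 7.6² / 4.14² = 52.9, rounded up to 53.

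The total is 106, an exact match with no loss built in. A t-test calculation gives 54 per arm, 108 in total. A one-sided test gives 84 in total and does not match. So 106 is the number needed before dropout.

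**Step 2. Find what leads to 127.**

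- 106 × 1.2 = 127.2, which rounds to the stated 127.
- 106 / (1 − 0.20) = 132.5, which rounds up to 133. Rounding up within each arm gives 53 / 0.8 = 66.25, so 67 per arm and 134 in total.

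The gap between 127 and 133 is 6 children, or 6 / 127 = 4.7%, which is more than rounding.

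**Step 3. Completers expected from 127.**

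- 127 × 0.8 = 101.6, against 106 required: a shortfall of 4.4.
- Largest dropout that still leaves 106: 1 − 106 / 127 = 16.5%.
- Check on the corrected target: 133 × 0.8 = 106.4.

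**Step 4. Power on the same inputs** (difference 4.14, SD 7.6, two-sided 0.05, equal arms).

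| Completers | Normal approximation | t-test |
|---|---|---|
| 106 | 80.1% | 79.3% |
| 101.6 | 78.4% | 77.6% |
| 106.4 (133 enrolled) | 80.2% | 79.5% |

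**Step 5. Compare with the stated duration.** At 60 per year, 127 children take 127 / 60 = 2.12 years. The stated 2.2 years corresponds to 60 × 2.2 = 132 children, and 106 / (60 × 0.8) = 2.21 years. The duration therefore fits division by 0.8 more closely than it fits 127. This is supporting evidence only.

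**The case against.** **The planned analysis is not a completers' t-test.** Statistical Considerations specifies a constrained longitudinal mixed model with follow-up at 3 and 6 months, adjusted for age, sex and cancer type. Children lost before month 6 still contribute earlier data, and use of the baseline measurement reduces residual variance. The article gives no correlation r between baseline and 6 months, so r has to be assumed. With the usual variance factor 1 − r², power at 101.6 completers is about 78% at r = 0, 82% at r = 0.3 and 89% at r = 0.5. The loss is offset once r² reaches 1 − 101.6 / 106 = 0.0415, that is r of about 0.20. This is a fair point about the consequence: real power under the planned model may well exceed 80%. It does not rescue the target, because the Sample Size section does not use this gain. It sets a required headcount and an allowance meant to protect it, and the allowance is too small.

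**The power figures depend on reading 7.6 as a standard deviation.** True. If the SEM label is right, neither 106 nor 127 follows and the loss of under 2 points means little. The headcount argument does not depend on this: whatever lies behind 106, a 20% loss requires 106 / 0.8.

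**The 2.2 years proves nothing.** The rate is approximate (58 per year would give 127 / 58 = 2.19 years), and it counts diagnoses rather than enrolments. This stands, so the duration shows a loose fit with 127 and not which formula was used. The multiplication by 1.2 is likewise inferred from the match.

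**The effect is minor.** Also true: about 6 children and under 2 percentage points of power, with no effect on bias, type I error or the analysis.

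**Conclusion.** The point holds. Required number, dropout rate and target are all stated, and they do not agree: 127 leaves 101.6 children at the assumed 20% loss and secures 106 only if dropout stays at or below 16.5%. The consistent target is 133, or 134 with equal arms. That part is arithmetic on the protocol's own figures and needs no further assumption.

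The accompanying fall in power, from 80.1% to 78.4% (79.3% to 77.6% by t-test), holds for an unadjusted two-sided comparison with 7.6 kg as the standard deviation. The mixed model could recover this amount or more, but the protocol makes no such case for 127. The consequence is small. It is worth correcting because the figure is the headline target and the stated 80% power rests on it.

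**What to change.** Choose one of two corrections and use it in both the abstract and the Sample Size section.

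1. State the target as 133, or 134 for equal arms. This costs 6 or 7 more children. At 60 per year that takes 133 / 60 = 2.22 or 134 / 60 = 2.23 years, in line with the 2.2 years already given.
2. Keep 127 and state that it gives about 78% power at 20% dropout, or 80% power if dropout does not exceed 16.5%. This needs no extra patients, only a slightly less favourable statement.

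In either case, print the dropout formula, say that the test is two-sided, and reconcile the recruitment duration with the chosen target. The SEM label on 7.6 should be resolved at the same time, because the quoted power figures depend on it. If the sponsor prefers to defend 127 through the mixed model, the assumed baseline-to-6-month correlation and the resulting power need to be stated.

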### Statistical Considerations

Constrained longitudinal data analysis is applied to evaluate the intervention effectiveness by using constrained (generalized) linear mixed models in two scenarios. In the first one, predictors will include follow-up time points categorized as 3 and 6 months to account for any non-linear effect and dummy variables representing the intervention group at 3- and 6-month follow-ups, respectively. In the second scenario, the time variable will be treated as a continuous variable and an interaction between treatments (binary-coded, 1 representing intervention group), and the time variable will be included instead. Normal distribution will be applied on continuous outcome muscle strength, while binomial distribution will be applied on binary outcome metabolic syndrome. Baseline characteristics, such as age (as a continuous variable), gender, and type of cancer (categorized as solid, CNS, and hematologic tumors), will be included additionally as covariates in both scenarios. Patient identity will serve as a random intercept. Likelihood ratio tests based on maximal likelihood will be applied for the model selection of the fixed effects to determine linear or non-linear associations. Benjamin-Hochberg procedure will be applied to reduce the false discovery rate due to multiple comparisons. The level of significance is 0.05.

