The study is based on the overarching hypothesis that supervised structured integrative neuromuscular training initiated at the time of diagnosis effectively prevents deficits in muscle strength 6 months after initiated treatment.

The primary objective of this study is to investigate the effects of a 6-month integrative neuromuscular training intervention compared with unsupervised home-based exercise on isometric knee extension strength in children and adolescents (6–18 years) during anti-cancer treatment. Our secondary objectives are to investigate the effects of the intervention on markers of metabolic syndrome, days of hospitalization, health-related quality of life, upper-body muscle strength, exercise capacity, physical function, physical activity behavior, and body composition.

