### Eligibility Criteria

Children and adolescents with newly diagnosed malignant and benign neoplasia aged 6–17.9 years and admitted from January 2021 for treatment at the departments for pediatric oncology will be eligible for inclusion. Diagnoses include malignant and benign neoplasia treated with chemotherapy and/or irradiation. Children with a severe mental and/or physical disability (i.e., participants where all types of physical training and testing of physical function are contraindicated), terminal illness, and individuals unable to communicate in Danish will be excluded.

When answering patient-reported outcomes, the parent(s) will be used as informants to answer proxy questionnaires and provide sociodemographic data on behalf of their child.

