#### Primary Secondary Outcome

##### Markers of Metabolic Syndrome (Primary Secondary Outcome)

Metabolic syndrome is based on waist circumference, triglycerides, high-density lipoprotein (HDL) cholesterol, blood pressure, fasting blood sugar, and insulin. Age-based criteria for each parameter concerning metabolic syndrome is defined by the International Diabetes Foundation (67).

Waist circumference is measured in centimeters, after taking several consecutive natural breaths, at a level parallel to the floor, in a midpoint between the top of the iliac crest and the lower margin of the last palpable rib in the midaxillary line following standards described by the World Health Organization (68).

Triglycerides, high-density lipoprotein (HDL) cholesterol, fasting blood sugar, and insulin will be analyzed in blood samples drawn from an antecubital vein or, when possible, through a central or peripheral venous catheter. Samples that have already been collected for routine clinical or research purposes (and stored in an authorized biobank) will also be used in the study to minimize the number of samples taken.

Blood pressure (mmHg) will be measured in the morning using the right arm with the subject sitting.

Although children younger than 10 years cannot be diagnosed with metabolic syndrome, the potential decline or increase in the biological markers (i.e., predisposition for metabolic syndrome) will be investigated in this study.

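### The only model named for the top-ranked secondary outcome is for a yes/no diagnosis that, by the protocol's own account, cannot be made in enrolled children under 10

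*Protocol article*

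**What the plan says.** The objectives, at the end of the Introduction of the protocol article, include the aim to "investigate the effects of the intervention on markers of metabolic syndrome". The Outcomes section ranks these markers first among the secondary outcomes and lists the components: waist circumference, triglycerides, HDL cholesterol, blood pressure, fasting blood sugar and insulin. On classification it says: "Age-based criteria for each parameter concerning metabolic syndrome is defined by the International Diabetes Foundation". It closes with a limit and a commitment. The limit is "Although children younger than 10 years cannot be diagnosed with metabolic syndrome". The commitment is that "the potential decline or increase in the biological markers (i.e., predisposition for metabolic syndrome) will be investigated in this study".

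Statistical Considerations plans constrained (generalized) linear mixed models. It assigns the normal distribution to muscle strength and then says "binomial distribution will be applied on binary outcome metabolic syndrome". It names no model for the markers and does not restrict the binomial model by age. Age appears only among the covariates: "Baseline characteristics, such as age (as a continuous variable), gender, and type of cancer".

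Eligibility Criteria admits children with "newly diagnosed malignant and benign neoplasia aged 6–17.9 years".

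**The concern.** The outcome is described as a set of measured quantities, but the model named for it analyses a diagnosis. For children aged 6 to 9 that diagnosis does not exist on the protocol's own terms, so the binomial model has nothing valid to analyse in them. Either they leave the analysis, or they enter as certain non-cases in both arms.

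The first choice answers the top-ranked secondary question in a subset of the randomized children. The second mixes in children whose result is fixed in advance and dilutes the difference in risk between the arms. A continuous age covariate does not help: it adjusts for age but cannot supply a missing definition.

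The form of the outcome is also left open. An analysis plan that follows Statistical Considerations gives a binary endpoint. One that follows the Outcomes section gives continuous markers. For the highest-ranked secondary outcome, that choice should be made before anyone sees the data by arm.

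**Working it through.** **1. The plan's own figure.** The article gives no sample size, event rate or age distribution for metabolic syndrome. Its only calculation is for knee-extension strength, and it reproduces if 7.6 kg is used as the standard deviation. With a difference of 10% × 41.4 = 4.14 kg, two-sided alpha 0.05 and 80% power, n per arm = 2 × (1.96 + 0.84)² × 7.6² / 4.14² = 2 × 7.84 × 57.76 / 17.14 = 52.8. That rounds up to 53 per arm, or 106 in total. The planned total of 127 is 106 × 1.2. Neither figure speaks to this outcome; 106 and 127 are used below only as denominators.

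**2. The statements side by side.**

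| Question | Outcomes section and Introduction | Statistical Considerations |
|---|---|---|
| What is the outcome? | Markers of the syndrome | The syndrome, yes or no |
| Can it be determined under age 10? | Diagnosis no, markers yes | Not addressed; no age limit |
| Which model? | None named | Binomial mixed model |

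Enrolment starts at age 6, so ages 6 to 9 lie inside the trial and outside the diagnosis.

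**3. How many children.** The share under 10 is not in the article, so it is an assumption here.

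- Uniform ages over 6 to 18: (10 − 6)/(18 − 6) = 33.3%, and 127 × 0.333 = 42.
- Uniform ages over 6 to 17.9: 4/11.9 = 33.6%, and 127 × 0.336 = 43.

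| Assumed share under 10 | Of 127 enrolled | Of 106 evaluable |
|---|---|---|
| 20% | 25 | 21 |
| 33% | 42 | 35 |
| 50% | 64 | 53 |

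**4. Effect of counting them as non-cases.** Let f be the share under 10, equal in the two arms, and let p1 and p2 be the risks in children aged 10 or over. The risk in each whole arm is (1 − f) × p, so the risk difference becomes (1 − f) × (p1 − p2): it shrinks by exactly f. For an illustrative difference of 0.15, it becomes 0.80 × 0.15 = 0.12 at f = 20%, 0.10 at one third, and 0.50 × 0.15 = 0.075 at 50%. The risk ratio is unchanged, because (1 − f) cancels.

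**5. Effect of leaving them out.** The risk difference in older children is kept, but the sample falls to 127 × 0.80 = 102 at f = 20%, about 85 at one third, and 64 at 50%, before dropout.

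**6. Children who cross the boundary.** With uniform ages, those aged 9.5 to 10 at baseline make up 0.5/12 = 4.2%, about 5 of 127. They turn 10 by month 6, so the diagnosis becomes definable for them between visits. Any age restriction has to say at which date age is taken.

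**The case against.** The best defence is that the sentence in Statistical Considerations illustrates how distributions are matched to outcome types. Read as a complete list, it would also leave peak oxygen uptake, walking distance, body composition and quality of life without a model. On the milder reading, continuous markers would take the normal model, and the Outcomes section does promise to study their change. This is also a condensed article: the full protocol and any analysis plan are not shown, and who enters a given model is the sort of detail they commonly settle.

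Part of this stands. A reader might infer that the trial will not analyse the markers at all, or that young children are ignored. The article does not support that, since it commits to investigating marker change. Nor does it say that children under 10 will be excluded or counted as non-cases; that follows from applying a binary model to them and is not a stated plan.

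What does not fall away is the conflict. Statistical Considerations does not merely omit a detail. It names metabolic syndrome and fixes its form as binary, without an age limit, while the Outcomes section says that form is unavailable for some of the eligible children.

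Two further inferences should be resisted. One is that a third of the sample is known to be affected; that rests on a uniform age distribution. The other is that this problem is what leaves the outcome underpowered, or that the model will fail to converge. The article gives no event rates, and the trial is not powered on this outcome. With assumed risks of 30% and 15% and 53 per arm, a simple two-proportion test has only 46% power even if every child could be classified, against 30% to 32% with a third counted as non-cases or left out. Much of the shortfall would exist anyway.

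**Conclusion.** The point holds as an internal inconsistency. The top-ranked secondary outcome is defined through continuous markers, but the only model named for it needs a diagnosis that the protocol says cannot be made under age 10, in a trial that enrols from age 6. About 25 to 64 of 127 children are affected if 20% to 50% are under 10, and 42 to 43 if ages are uniform. These shares are assumptions. The contradiction itself depends on none of them. Counting the younger children as non-cases reduces the risk difference by their share.

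The weight is moderate. A reader might take this as a flaw that undermines the trial, but the primary outcome, the sample size and the randomization are untouched, and the marker data are to be collected at all ages. It is worth correcting because it concerns the first secondary question and costs little to settle before the data are seen by arm.

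**What to change.** In Statistical Considerations, make the main analysis of this outcome the continuous markers (waist circumference, blood pressure, triglycerides, HDL cholesterol, fasting glucose and insulin) in all randomized children, with the constrained linear mixed model already planned. Choose one of two forms in advance:

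- each marker analysed separately, under the Benjamini-Hochberg procedure already stated; or
- one prespecified score built from age- and sex-standardised markers, with HDL reversed.

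Keep the binomial model for the diagnosis as a supportive analysis, restricted to children aged 10 or over at baseline. Fixing age at baseline keeps the same children in the analysis at every visit and settles the case of those who turn 10 during follow-up.

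The cost is mainly wording, because every component is already measured. Separate markers mean several tests in place of one. A score gives a single test, but it is less familiar to readers than a diagnosis and needs reference values that the article does not supply.
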